### Recruitment

Participants will be enrolled into the trial over a 27-month recruitment period, yielding a rate of ~16 participants/month. The planned enrollment period will begin January 2013 and conclude in April 2015. Women will be enrolled in consecutive “waves” of ~n=50 for efficient use of personnel and resources across the study period and to test women close to the start and end of exercise classes. The primary method of recruitment will be through mailings from the Oregon State Cancer Registry (OSCaR), a population-based tumor registry run by the Department of Human services that collects and analyzes information on cancer cases in Oregon. The registry will send an information letter to all living female cancer survivors with eligible diagnoses, between the ages of 50 and 75 years old and within a 30 mile radius of the intervention sites that describes the study and asks them to return a pre-paid response form indicating their willingness to be contacted. Additional recruitment strategies include direct referral through oncology providers at OHSU and other local clinics and direct community recruitment using newspaper ads, radio, announcements on websites, as well as presentations at cancer support groups and cancer-related conferences.

### Procedures

Interested women are screened and those eligible are scheduled for an appointment where they will provide written consent and undergo baseline data collection All data collection is conducted according to standard operating procedures. Participants complete questionnaires first followed by testing for postural stability, physical function, and maximal muscle strength. This testing order is designed to minimize the impact of fatigue on performance measures and is used for the baseline, 3 month, 6 month and 12 month data collection visits. Falls are tracked by each participant on a daily log that is collected by study staff each month.

### Randomization and blinding

After completing baseline testing, each participant will learn her group assignment by receiving a sealed, sequentially numbered envelope from the project director and opening the envelope that contains the group assignment randomly assigned to her sequence number. The sequence numbers are generated by a statistician using MS Excel. Measurement technicians who are responsible for data collection and for coding falls data are blinded to participant group assignment.

### Study interventions

Participants in each study group will attend supervised 1-hr classes, twice weekly for 6 months. It is expected that women with mixed employment status will enroll in the study so daytime and early evening classes will be offered. At each site, a certified exercise instructor trained by the study team will lead classes. Each intervention minimizes reliance on expensive equipment and uses simple, easily performed exercises based on functional movements. It is difficult to precisely equilibrate the total volume (intensity and duration) of exercise performed between experimental groups because the nature of each modality is so different. Both will be matched as closely as possible in progression from the low to high end of the range for moderate intensity. Instructors will work with the study investigators and project director on a monthly basis to refine individual participant efforts based on individual tolerance and to adjust their training progression.

### Strength training

The strength training program used in this study is based on training programs that improved neuromuscular function (strength, gait, and balance) and reduced fall risk factors in our prior studies in women without cancer [44,45] and in our recently completed trials in BCS. This program complies with the American College of Sports Medicine (ACSM) exercise guidelines for cancer survivors [46] and with ACSM recommendations for progressive resistance training for novice weightlifters and older adults for 1–3 sets of 8–10 exercises at a weight that can be done for 8–12 repetitions (approximately 60-80% of 1-rep max) with 1–2 min rest between sets [47]. The strength training intervention will use weighted vests to apply resistance during lower body exercises and steps to increase height during stepping routines*.* Lower body strengthening exercises using functional movement patterns that challenge balance by using muscle groups and movement involved in everyday activities (chair rises, 90-degree squats, side-to-side squats, toe raises, lunges (forward, lateral, backward, walking), multi-directional step ups) will comprise the study program. The intensity of strength exercises, set by the amount of weight in the exercise vest (expressed as a percent of body weight) will increase from 4% of body weight to 15% of body weight and duration for each exercise will range from 1–3 sets of 8–15 repetitions. Training is progressive, where intensity will increase by 2%-3% of body weight per month, sets will increase by ~1 set every 2 months and repetitions will decrease from the high to the low end of the range as intensity and sets increase.

### Tai chi

The Moving for Better Balance program [48] will be the Tai Chi intervention to in this study. The protocol consists of a set of purposeful and functional movement forms blended with practice variation and therapeutic moves developed on the basis of prior studies [22,49-51]. Because the goal of the exercise is to assist patients in retaining postural stability and mobility, the protocol is specifically designed to challenge balance control and train gait patterns, as reflected in movements such as ankle sways, displacement of the body's center of mass over the base of support, trunk rotation/flexion, coordinated eyes-head movements, and multi-lateral stepping. The only resistance applied during exercise will be the participant's own body weight. The early stage of the program (i.e., the first 10–12 weeks) emphasizes primarily learning and practicing single and integrated forms/movements with multiple repetitions. The later stage focuses on performing and exercising integrated forms, variation in forms, and therapeutic moves to improve movement coordination, postural balance, sensory integration, and locomotion. Natural breathing is also emphasized as part of the exercise and integrated into the tai chi movement routine. Training is progressive with the number of forms doubling and repetitions increasing by ~2-4 each month for the first 3 months and the complexity of forms gradually increasing thereafter.

### Stretching control

Participants in the control group will attend a supervised stretching program of the same frequency, duration, and length as the tai chi and strength training groups. During stretching, participants will perform a series of whole body flexibility (stretching) and progressive neuromuscular relaxation exercises. Stretching exercises will be performed according to the ACSM guidelines for flexibility exercise: static stretching that emphasizes major muscle groups with 3–4 repetitions of each stretch held to the point of mild tension but not pain for 10–30 seconds [52]. Stretches will be performed from a seated or lying position in order to minimize weight-bearing forces that might increase muscle strength or postural control. The stretching will also be limited in duration to 15–20 minutes, with the remainder of the class devoted to relaxation exercises that produce no neuromuscular stimulus. Many exercise trials in older adults, including ours and including studies with falls as an outcome, have used a flexibility training control condition and results have shown no effect of this training on outcomes associated with tai chi or strength training [36,53-56]. A recent ACSM Roundtable issuing exercise guidelines for cancer survivors recommended “avoidance of inactivity” among cancer survivors to optimize quality of life [46]. Stretching and relaxation exercise increases range of motion, promotes a sense of wellbeing and may be viewed as a beneficial exercise program for participants randomized to this group. We are including a measure of flexibility in our list of outcomes in order to assess the potential benefit of the stretching program and provide an incentive to participants in this group by including a measure that could improve from stretching exercise.

### Participant safety and side effects

Though injuries associated with any of the study exercise programs have been minimal in prior reports, as with any form of exercise there is a slight risk of injury. The following steps will be taken to reduce the risk of injury and symptoms/side effects that might limit exercise adherence, including: 1) required physician clearance for every enrolled participant, 2) monitoring and early care of musculoskeletal symptoms by the study team that includes an expert in care and prevention of sports-related injuries, and 3) minimizing risk of lymphedema through individually tailored exercise programs, instructor and participant education, and regular monitoring for signs and symptoms. If a participant experiences a cancer recurrence over the course of the study data collected after her recurrence date will be excluded from analysis, but she can continue in the study program with physician clearance.

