### Power and sample size

The sample size is powered to address the primary study aim to reduce falls. In older adults, 30% of community-dwelling elders are likely to fall within 1 year [37] and Li and others have reported a reduction in fall risk of 47% from 3 [38] or 6 [22] months of tai chi exercise. This effect size provided a realistic estimate of the expected reduction in fall risk and was used as the basis for power analyses. The required sample to test the primary hypotheses in a negative binomial regression model [39] was determined with the following assumptions:, alpha=.05, 25% shared variance (R [2]=.25) among the dummy vectors representing treatment, and an overdispersion parameter (Phi) of 2.5. Under these assumptions a sample size of n=342 (n=114 per group) will provide 80% power to detect at least a 47% reduction in the fall rate over 1 year by being in the 2 experimental groups (tai chi and strength training) versus the control group. These estimates were generated using PASS 2008 [40]. To protect against an estimated attrition of 25% during the intervention period, 143 participants will be randomized per group (total sample size: N=429). The attrition estimate is based on attrition rates in yearlong studies of weighted vest strength training in BCS [41] and slightly higher than what has been observed in 1-year studies of older women without cancer participating in tai chi exercise [42,43] (19%-24%) or resistance exercise (24%) [43].

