### Data analysis plan

The univariate distribution of each variable will be examined to check for departure from normality and outliers [76]. For each analysis described below, each subject will be analyzed according to the group to which she was randomly assigned and regardless of missing data (i.e., intention to treat). Medical treatment changes and cancer recurrence during the study will be tracked and used to describe the sample and document why participants may not have completed the study. In the unlikely event of a large subgroup, these data could be used for exploratory sub-group analysis to suggest directions for future research. Age, cancer type (breast or other), and time since cancer treatment completion, will be included as covariates in all analyses.

A negative binomial regression model will be used to test the efficacy of tai chi and strength training (versus stretching control) in reducing the total number of falls per participant that occur during the intervention period (from baseline to 6 months). Negative binomial regression is preferred over Poisson regression for modeling the count data because of the overdispersion that is common with actual research data [40,77]. Intervention type will be entered into the model as 2 dummy vectors, with the reference group being the control group. Fall rates for participants who drop out of the study will be adjusted by accounting for their exposure time within the study timeframe. A significant incidence rate ratio (IRR) less than 1.0 for the dummy vector representing tai chi and/or strength training would provide support for the hypothesis that the respective intervention reduced the rate of falls compared to the control group (controlling for covariates).

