The persistent effects of the intervention on fall outcomes after formal training stops will be evaluated with a piecewise intent-to-treat negative binomial regression model with the change point occurring at 6 months. Of particular interest is whether the IRRs for the treatment groups differ after the change point. In addition, the moderating effect of participation in an exercise program following the end of the intervention will be examined. Specifically, exercise programs engaged in for least 50% of the follow-up period will be categorized and dummy coded (e.g., infrequent participation versus regular participation). These variables will be entered into a negative binomial regression model along with the product of these dummy vectors and treatment (i.e., interaction effects). Significant interaction effects indicate that continued participation modifies the effect of the intervention on fall rate. With this analytic approach we will be able to determine whether the benefits of the exercise interventions persist with and without continued participation in an exercise program, and whether control participants who begin programs similar to the intervention programs show improvements on the fall rate outcome.

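### Excluding data collected after a cancer recurrence departs from the intention-to-treat analysis the plan claims, and the end of exposure for women who recur and continue is not specified

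*Protocol article*

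**What the plan says.** Three statements in the protocol article bear on this point.

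- **Participant safety and side effects.** After a recurrence, "data collected after her recurrence date will be excluded from analysis, but she can continue in the study program with physician clearance". The rule covers data of every kind and applies whether or not she goes on attending.
- **Data analysis plan, opening paragraph.** For each analysis, "each subject will be analyzed according to the group to which she was randomly assigned and regardless of missing data (i.e., intention to treat"). Recurrence appears here in another role: "Medical treatment changes and cancer recurrence during the study will be tracked and used to describe the sample", to document why women did not complete and, if a large subgroup arose, to support exploratory subgroup work. The exclusion is not mentioned.
- **Data analysis plan, primary and persistence models.** The primary outcome is the "total number of falls per participant that occur during the intervention period (from baseline to 6 months"). On exposure: "Fall rates for participants who drop out of the study will be adjusted by accounting for their exposure time within the study timeframe". The persistence analysis is a "piecewise intent-to-treat negative binomial regression model with the change point occurring at 6 months". Neither model description refers to recurrence.

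**The concern.** Intention to treat asks what happened to everyone randomized, over the whole window, whatever occurred along the way. Recurrence occurs after randomization. A rule that sets aside falls reported after it changes the question to the fall rate while women remain recurrence-free. That may be a legitimate question, but it is not the one the analysis plan names, and someone reading only the Data analysis plan would not learn that data are discarded.

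The discarded months are probably not typical. The Background argues that the disease or its treatment is the likely cause of the rise in falls after diagnosis. By that reasoning, time after a recurrence is plausibly time at higher risk.

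There is also a gap in the exposure rule. A woman who recurs and stays has not dropped out, so the one stated adjustment does not plainly reach her. If her later falls were removed while her later months stayed in the offset, her fall rate would be understated.

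**Working it through.** **Text comparison.** The safety section excludes post-recurrence data from analysis. The Data analysis plan claims intention to treat for each analysis and again for the persistence model. The woman stays in her assigned arm and her earlier data are used, so the rule amounts to censoring at recurrence. Censoring at a post-randomization event, when later outcomes have been collected, gives a while-recurrence-free effect. The label and the rule therefore describe different estimands.

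**Size.** There is no planned figure to reproduce, because the article gives no recurrence rate. Everything below is illustrative, works with aggregate rates and is not a fitted negative binomial model.

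Inputs from the article: 429 women ("To protect against an estimated attrition of 25% during the intervention period, 143 participants will be randomized per group (total sample size: N=429")), a six-month primary window, and a planned 47% reduction, that is a rate ratio of 0.53. Assumptions: a proportion r recurs within six months, r = 1% to 5%, with timing uniform, so half the window is lost on average.

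- Women affected = 429 × r.
- Person-months discarded = 429 × r × 3, out of 429 × 6 = 2574.
- Factor on an arm's fall rate if falls are dropped, exposure is left uncut and risk does not rise = 1 − r/2.
- Factor on the rate ratio if one arm has r and the other r/2 = (1 − r/2)/(1 − r/4).

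| r | Women | Person-months | Rate factor | Rate-ratio factor |
|---|---|---|---|---|
| 1% | 4 | 13 | 0.995 | 0.997 |
| 3% | 13 | 39 | 0.985 | 0.992 |
| 5% | 21 | 64 | 0.975 | 0.987 |

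With equal recurrence in the arms, the rate factors cancel in the rate ratio. At 5% against 2.5%, a true 0.53 becomes 0.53 × 0.987 = 0.523 if the exercise arm has more recurrences, or 0.53/0.987 = 0.537 if the control arm does.

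**If the fall rate doubles after recurrence** (a further assumption):

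- Share of all falls discarded = r × 0.5 × 2/(1 + 0.5r), which is 1.0% at r = 1% and 4.9% at r = 5%. This is a share of events lost, not a bias in the rate ratio.
- At 5% against 2.5% with exposure properly cut at recurrence, the rate ratio differs from the intention-to-treat one by (1 + 0.0125)/(1 + 0.025) = 0.988. This is the gap between the two estimands alone.
- With exposure uncut as well, the factor is 0.987 × 0.988 = 0.975.

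**Persistence model.** Women who recur before month 6 contribute nothing after the change point. If a further proportion r recurs in months 6 to 12, the share of that segment lost is about r + r/2 = 1.5r, or 1.5% to 7.5% on the same assumptions.

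**The case against.** The strongest defence is that the analysis plan spells out its own intention to treat: analysis as randomized, regardless of missing data. Under the exclusion rule no woman is removed or moved to another arm. Eligibility is limited to women who have finished chemotherapy and have no concurrent adjuvant therapy other than hormone manipulation for breast cancer, so an arm-neutral cut-off fixed in advance, at the point where a woman may leave that population, is a defensible estimand. This stands as an argument for the recurrence-free estimand. It does not make that estimand intention to treat, because the data in question are collected and then set aside rather than missing.

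A reader might infer three stronger things that the document does not support:

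- **That her later months will be counted as fall-free time.** The safety section excludes all later data, which can as easily be read as ending the follow-up those reports represent. The exposure sentence names women who drop out but does not say that nobody else is adjusted. Counting the months is one possible reading, and how the offset treats other shortened follow-up is detail an article may leave to the full plan.
- **That the analysis plan confines recurrence to description.** It also uses recurrence to explain non-completion and, possibly, for an exploratory subgroup.
- **That the treatment effect will be materially biased.** Nothing suggests recurrence would differ by arm, and the effect is small even when it is assumed to.

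It is also fair to say that keeping post-recurrence falls has a weakness: continuing is permitted, not assured, so those falls come from women who go on reporting.

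**Conclusion.** The point holds as a mismatch between the stated rule and the stated estimand. The exclusion in the safety section departs from the intention-to-treat analysis claimed for each analysis and for the persistence model, and yields a while-recurrence-free effect instead. The end of exposure for a woman who recurs and continues is unspecified.

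The numerical stake is small. With recurrence assumed at 1% to 5% over six months, the effect cancels in the rate ratio when recurrence, and any rise in risk after it, are alike across arms. At 5% against 2.5% the factor is about 0.987 with exposure uncut and no rise in risk, and about 0.975 if the fall rate also doubles after recurrence. The recurrence rates, the imbalance and the doubling are assumptions; the article supplies none of them. The reason to act is that the plan should estimate what it says it estimates, and that correcting this is nearly free.

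**What to change.** Reconcile the safety section with the primary and persistence paragraphs of the Data analysis plan before unblinding, in one of two ways.

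- **Preferred.** In the primary intention-to-treat analysis, keep all falls reported through the analysis window regardless of recurrence, with exposure running to the last report. Add a sensitivity analysis that censors both falls and exposure at the recurrence date. Reword the exclusion sentence so that it applies to that sensitivity analysis, and treat the persistence model in the same way.
- **Alternative, if the sponsor prefers the exclusion.** Drop the intention-to-treat label for the affected analyses, state the while-recurrence-free estimand, and say that exposure ends at the recurrence date.

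Neither option affects whether a woman continues in her program. The cost is a sentence or two of text and, under the first option, one extra model run; falls are already tracked on daily logs collected monthly. The remaining limitation of the first option, that post-recurrence falls come only from women who continue reporting, should be stated with the result.

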### Six-month follow-up period

To evaluate the long-term effects of tai chi and strength training on falls and function, women will be followed for an additional 6 months after conclusion of the 6-month supervised intervention. Women will continue to track their falls during the follow-up period using the daily logs submitted each month (see Fall Surveillance below). During the follow-up period, we will obtain information about participants’ exercise using weekly logs. Women will be called at 1 and 3 months during the follow-up period to get verbal reports of their exercise logs and the weekly logs will be collected at the month 12 visit. We will consider participation in community and/or home-based exercise in the analysis for Aim 3 (see Analysis Plan) and will also repeat measures of strength and postural stability in order to better assess both the residual effects of the intervention programs among women who do not exercise in the follow-up period and the influence of continued exercise on strength and balance after formal training stops.

## Measures

### Primary outcome

Falls: In this study, a fall is defined as unintentionally coming to rest on the ground or at some other lower level, not as a result of a major intrinsic event (e.g., stroke or syncope) or overwhelming hazard [57]. Falls will be assessed retrospectively at baseline through 6-month recall to characterize the sample and check for equality of randomization. Falls will be assessed prospectively during the study by monthly reports completed through a web portal or returned by postal and/or electronic mail, methods proven successful in our 2 previous studies and by others, including [name] [3,4,22,58]. In our recently completed observation study of BCS (N=58), we obtained 98% of monthly fall reports over 6 months [3]. If a participant indicates a fall she will then be asked to detail any injury that resulted from each fall. A fall will be considered “injurious” if it results in fractures, head injuries, sprains, bruises, scrapes, or serious joint injuries, or if the participant seeks medical care [57]. Of interest in the study are the number of falls, the number of injurious falls, and medical care resulting from a fall during the intervention period.

